**Fig. 1 Fig1:**
[figure not shown]
Study workflow diagram

Our hypotheses are:Compared with the control groups, those in the AIDS Fighter · Health Defense intervention groups will have better ART adherence.Varying time to receive AIDS Fighter · Health Defense intervention may lead to varying ART adherence.AIDS Fighter · Health Defense could help newly diagnosed young people to maintain good long-term ART adherence.

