## Methods/Design

### Study design

A stepped-wedge design randomized controlled trial with four groups will be conducted. Which is a relatively new research design [37]. The design included an initial phase in which no groups are exposed to the intervention. Subsequently, at fixed time intervals (“steps”), a group (or set of groups) is randomly crossed over from the control to the intervention under evaluation. The start of the intervention is different for each group, and this design helps to verify the effect of intervention timing on intervention effect.

Participants will be assigned to the four groups in 1:1:1:1 randomly. There is no dedicated control group in this study, and each step group will receive AIDS Fighter · Health Defense intervention in turn as the trial progress (see Fig. 1 for study workflow diagram). The group which has not received the intervention will be treated as the control group. Data collection will be conducted before and after intervention in each group. Participants in each group will be evaluated for medication adherence after the first week of intervention and the other outcomes will be evaluated after the first month and third month of intervention. Follow-up evaluations for the same outcomes will be performed at 6 and 12 months after the end of the intervention.

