### The first step intervention group

The first step group will receive the intervention of the educational game “AIDS Fighter · Health Defense” through WeChat at the time of enrollment and will be required to play the game at least 5 days a week and 20 min a day. During the 3-month intervention, participants will receive daily message notifications that inform users to play the game. A data management system will be used to monitor participants' time in the game and check details of the participant's use of the game.

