### The 2-4 step intervention group

The intervention of 2-4 step groups will be same as the first step intervention group, but the time they receive AIDS Fighter · Health Defense will be different. The second step group will receive the intervention 1 week after starting ART. The third step group will receive the intervention 1 month after starting ART. The fourth step group will receive the intervention 3 months after starting ART.

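### Hypothesis 3 cannot be tested as an effect of the game against no game, because no unexposed participants remain at the 6- and 12-month follow-ups

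*Protocol article*

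**What the plan says.** In the Protocol article, the hypotheses at the end of Study design list three claims. The first is worded as a comparison with control groups. The second is that adherence may differ with the time of starting the game. The third is that the game "could help newly diagnosed young people to maintain good long-term ART adherence"; no comparator, external reference or adherence threshold is given for it.

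On controls, Study design states: "There is no dedicated control group in this study". It adds: "The group which has not received the intervention will be treated as the control group".

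On timing, the first group receives the game "through WeChat at the time of enrollment". Groups 2 and 3 follow at one week and one month of ART. The section on step groups 2 to 4 closes with the last crossover: "The fourth step group will receive the intervention 3 months after starting ART".

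The Background and the section on the first step group give a game period of 3 months. Study design then says: "Follow-up evaluations for the same outcomes will be performed at 6 and 12 months after the end of the intervention".

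Data analysis names generalized estimating equations, linear mixed models and mixed logistic models, and relies on difference-in-difference to remove time trends. It does not say which visits enter which model.

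**The concern.** To say that the game helps people maintain adherence is to say that adherence is better than it would have been without the game. That needs someone without the game at the same stage of ART. The design supplies such people only until the last group crosses over, and the visits that bear on hypothesis 3 come months later.

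The time trend cannot be assumed away. The Background cites mean adherence in China of 81.1% at one week of ART, 80.9% at one month and 68.3% at three months, and gives no figure beyond that. A level seen at month 9 or month 15 could therefore not be credited to the game or held against it. The risk is a report of sustained benefit that rests on an uncontrolled trend.

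**Working it through.** **Inputs.** Game start after ART start: 0, 1 week (7/30.4 = 0.23 month), 1 month and 3 months. Game duration: 3 months. Follow-up: 6 and 12 months after the end of the game. Group size (Sample size calculation): 140 / (1 − 0.20) = 175, and 4 × 175 = 700, as the protocol states. The argument does not depend on the rest of the sample size calculation.

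**Step 1: visit times in months since ART start.** End of game = start + 3; follow-ups = start + 9 and start + 15.

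| Group | Game | First follow-up | Second follow-up |
|---|---|---|---|
| 1 | 0 to 3 | 9 | 15 |
| 2 | 0.23 to 3.23 | 9.23 | 15.23 |
| 3 | 1 to 4 | 10 | 16 |
| 4 | 3 to 6 | 12 | 18 |

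**Step 2: participants not yet exposed, as randomised.**

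| ART time | Unexposed groups | Number |
|---|---|---|
| 1 week, before group 2 starts | 2, 3, 4 | 3 × 175 = 525 |
| 1 month, before group 3 starts | 3, 4 | 2 × 175 = 350 |
| 3 months, before group 4 starts | 4 | 175 |
| Any time after 3 months | none | 0 |

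The earliest long-term visit (month 9) falls 9 − 3 = 6 months after the last crossover.

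**Step 3: sensitivity to the follow-up clock.** If the 6 and 12 months were counted from the start of the game, the visits would fall at months 6, 6.23, 7 and 9, and at 12, 12.23, 13 and 15. The earliest is still after month 3, so the count is still 0 of 700.

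**Step 4: what the late data can identify.** Write mean adherence of group g at ART time s as N(s) + E_g(s), where N is the course without the game and E_g is the game's effect in that group.

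- *Within a group,* only the sum N(s) + E_g(s) is observed. No late observation has E = 0, so the two parts cannot be separated.
- *Difference-in-difference* is (change in exposed) − (change in unexposed). After month 3 the second term has no data.
- *Between groups at the same s,* the contrast is E_1(s) − E_4(s). It is zero if the effect is fully sustained in both groups, and also zero if there is no effect in either. It answers hypothesis 2, not hypothesis 3.

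**Step 5: if late visits were pooled under one constant effect.** Comparing group 4's change across its crossover with group 1's change over the same period gives E_4(late) − [E_1(late) − E_1(early)]. This equals a single effect E only if E_1 does not change with duration and E_4 equals E_1. Hypothesis 2 allows the effect to depend on start time, which conflicts with the second condition.

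**The case against.** The strongest reply is that hypothesis 3, unlike hypothesis 1, names no control. Read modestly, it asks whether adherence after the game holds up, and that can be estimated within groups. This stands in part. A reader might infer that hypothesis 3 is untestable in every sense, and the document does not support that: maintenance can be described. What cannot be recovered is the causal part carried by the idea of helping.

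A second reply is that every stepped wedge ends with all groups exposed, and that this protocol says so openly. True, and it is not a contradiction. It is a reason not to list a long-term effect of the game beside the controlled comparison. Nor can a statistical analysis plan repair it, since no analysis creates unexposed participants.

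A third concerns the pooled models. A reader might infer that the game effect will be biased by the late visits. The text does not establish this. It sets no analysis window, does not say that late visits enter the estimate for hypothesis 1, and defines controls as groups without the game. Step 5 is a conditional risk only.

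A fourth concerns early-versus-late comparisons at equal ART time. A reader might infer that the planned visits supply these directly. They do not: follow-up is tied to each group's own end of game, so visits fall at months 9, 9.23, 10 and 12, then 15, 15.23, 16 and 18. CD4 count and viral load in particular would need modelling over time or aligned visits.

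**Conclusion.** The point holds in a limited form. As a claim about the game against no game, hypothesis 3 has no comparator at either long-term follow-up: 0 of 700 participants are unexposed at ART months 9 to 12 and 15 to 18. The last randomised comparison with unexposed participants is at ART month 3, with group 4 as the control. The result follows from the stated start times, game duration and follow-up times, holds under either follow-up clock, and needs no assumption about effect size or dropout.

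Hypothesis 1 is not affected within the first 3 months, provided waiting groups are assessed at the same ART times as exposed groups. The text ties assessments to the intervention, and the figures that may show a common calendar are not available, so this is an assumption. Description of long-term adherence and comparison by start time remain possible.

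**What to change.** 1. Restate hypothesis 3 as descriptive: adherence, CD4 count and viral suppression at the 6- and 12-month follow-ups, by group, with confidence intervals. Say that no sustained effect against no game will be claimed.
2. State that the game-versus-no-game estimate, including difference-in-difference, rests on assessments up to 3 months after ART start, while at least one group is unexposed. Confirm that waiting groups are assessed at those times.
3. Use later visits only for the early-versus-late comparison of hypothesis 2. Model time since ART start, because the groups' visits fall at different ART times.
4. If later visits are nevertheless pooled, do not assume one constant effect across start time and duration of exposure.

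The cost is wording in the hypotheses and Data analysis, and a weaker long-term claim. The timing comparison also takes on modelling assumptions about the course of each outcome between unequal visit times. Testing the causal version would need a concurrent group without the game up to the late visits, which is a different design.

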### Intervention design

Participants will receive AIDS education from health workers and start ART when diagnosed of HIV and randomly assigned into four groups. The first step group to the fourth step group will receive AIDS Fighter. Health Defense in turn at the start of ART, one week after the star of ART, one month after the star of ART and three months after the star of ART. Assessments will be completed before the intervention and after the first week, first month, and third month of intervention, and then a one-year follow-up evaluation will be conducted. The intervention design is shown in Fig. 2.

**Fig. 2 Fig2:**
[figure not shown]
Intervention design

### The first step intervention group

The first step group will receive the intervention of the educational game “AIDS Fighter · Health Defense” through WeChat at the time of enrollment and will be required to play the game at least 5 days a week and 20 min a day. During the 3-month intervention, participants will receive daily message notifications that inform users to play the game. A data management system will be used to monitor participants' time in the game and check details of the participant's use of the game.

### The 2-4 step intervention group

The intervention of 2-4 step groups will be same as the first step intervention group, but the time they receive AIDS Fighter · Health Defense will be different. The second step group will receive the intervention 1 week after starting ART. The third step group will receive the intervention 1 month after starting ART. The fourth step group will receive the intervention 3 months after starting ART.

### Recruitment of participants

The participants in this study are newly diagnosed young people with HIV. On-site recruitment will be conducted in AIDS clinics in Sichuan Province, China, where there are more than 10000 newly diagnosed people a year [38]. The inclusion criteria are: 1) diagnosed with HIV within 30 days [18]; 2) Young people aged 15 to 24; 3) Participants have clear consciousness and are able to read and communicate; 4) Participants were informed and voluntarily participated in the study; 5) Parental consent will be required to use the game if the participants are under 18 years old. And adults need to declare that they can use the game when they sign the informed consent. Those who have played similar games before will be excluded from the study. When the participants meet the inclusion criteria and agree to join this research, informed consent form will be signed.

### Sample size calculation

The sample size was performed using the formula developed by Hemming [39]. The basic parameters for sample size calculation are based on the mean rate of adherence to ART at one week (81.1%) [9], assuming that the ART adherence of the intervention group would reaches 95%. The significance level of the test is α=0.05, the test power is 1-β=0.9, the coefficient of variation is ρ=0.15, the number of observation periods is t+1=7, the number of steps is t=6, the number of clusters is k=4, and N1 is calculated based on the sample size of the two groups. PASS software was used to calculate the initial sample size N1=220. According to the following formula:$$\begin{array}{c}a=2k\left(t-\frac{1}{t}\right)\rho \left(1+\frac{t}{2}\right)\\ b={3N}_{1}\left(1-\rho \right)\rho \left(1+t\right)-2k\left(t-\frac{1}{t}\right)\left(1-\rho \right)\\ \begin{array}{c}c={3N}_{1}{\left(1-\rho \right)}^{2}\\ m=\frac{-b\pm \sqrt{{b}^{2}-4ac}}{2a}\\ N=\mathrm{m}\times \left(t+1\right)\times k\end{array}\end{array}$$

The required sample size for each group is calculated to be 140. Considering a potential 20% loss to follow-up, the final sample size for each group is 175, and the total sample size is 700.

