### Randomization and allocation concealment

Opaque envelopes will be used for randomization. Among the 700 envelopes, each envelope contained a note with the words "First Step Group", "Second Step Group", "Third Step Group" and "Fourth Step Group" (175 envelopes per group). An opaque envelope will be selected for the first time the participant enrolled, and they will be assigned to the corresponding group according to the envelope. The health workers for the AIDS education of newly diagnosed young people with HIV and the data analysts will be blinded for the allocation.

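### The 140 per group at 90% power comes from a six-step cluster formula, but the trial randomises individuals to four arms with four start times

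*Protocol article*

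**What the plan says.** The Sample size calculation section of the protocol article takes 81.1% adherence without the game (a one-week figure) and 95% with it. "The significance level of the test is α=0.05, the test power is 1-β=0.9". It adds "the coefficient of variation is ρ=0.15", and then "the number of observation periods is t+1=7, the number of steps is t=6, the number of clusters is k=4". A two-group size N1 = 220 is fed into a quadratic for m, and the total is N = m × (t+1) × k. The result is: "The required sample size for each group is calculated to be 140". Allowing for 20% loss, this becomes 175 per group and 700 overall.

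The design sections describe something else. Study design: "Participants will be assigned to the four groups in 1:1:1:1 randomly". Randomization and allocation concealment: "An opaque envelope will be selected for the first time the participant enrolled, and they will be assigned to the corresponding group". There are 700 envelopes, 175 for each group. Intervention design and the two sections on the step groups give four start times: at the start of ART, and one week, one month and three months later. Nothing in the text names a clinic or other cluster as the randomised unit.

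**The concern.** A sample-size statement should let a reader see what the trial can detect. This one differs from the trial in its unit of randomisation, its number of steps and the meaning of its total.

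- **Unit.** With individual allocation, k = 4 can only stand for the four arms. An intracluster correlation of 0.15 then has no cluster to refer to. The text also calls ρ a coefficient of variation, although it enters the formula as a correlation.
- **Steps.** Four groups with four start times give four steps, or three if the start at enrolment is not counted as a crossover. With four clusters and six steps, at least two steps would have nothing crossing over.
- **Total.** m × (t+1) counts observations summed over periods. The protocol reads it as a number of people, each of whom is then measured repeatedly.

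At stake is whether the quoted 90% power and the required 140 can be relied on in the report of the primary comparison.

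**Working it through.** **Inputs** (Sample size calculation): p1 = 0.811, p2 = 0.95, α = 0.05, power 0.90, ρ = 0.15, t = 6, k = 4, N1 = 220. Sidedness is not stated; I assume two-sided.

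**1. N1.** With unpooled variance, n = (1.960 + 1.282)² × (0.811×0.189 + 0.95×0.05) / 0.139² = 10.507 × 0.20078 / 0.019321 = 109.2. That is 110 per arm and 220 for two, so N1 reproduces. With pooled variance it is 113 per arm.

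**2. The quadratic as printed.**
- a = 2×4×(6 − 1/6)×0.15×(1 + 3) = 28.0
- b = 3×220×0.85×0.15×7 − 2×4×(6 − 1/6)×0.85 = 589.05 − 39.67 = 549.38
- c = 3×220×0.85² = 476.85

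All three are positive, so both roots are negative: −18.71 and −0.91.

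**3. Sign corrected** (a = −28.0, which is the same as reversing b and c). m = (549.38 + √(549.38² + 4×28.0×476.85)) / 56 = (549.38 + 596.01) / 56 = 20.45. Then 20.45 × 7 = 143.2 per group. Cutting m to 20 gives 20 × 7 = 140, exactly the stated figure. Rounding up to 21 would give 147. The loss step is correct: 140/0.8 = 175, and 175 × 4 = 700.

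**4. Same formula with steps that fit four start times** (internal-consistency check only).

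| t | a | b | m | m×(t+1) per group |
|---|---|---|---|---|
| 6 | −28.0 | 549.38 | 20.45 | 143.2 |
| 4 | −13.5 | 395.25 | 30.44 | 152.2 |
| 3 | −8.0 | 318.47 | 41.25 | 165.0 |

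**5. Power for individual randomisation.** Assumptions: a binary adherent/non-adherent endpoint, a two-sided test with pooled null variance, and 140 evaluable per arm.
- One arm against another, 140 vs 140: mean proportion 0.8805; null SE = √(0.8805×0.1195×2/140) = 0.03877; alternative SE = √(0.20078/140) = 0.03787; z = (0.139 − 1.960×0.03877)/0.03787 = 1.664; power 0.952.
- First step group against the other three at week 1, 140 vs 420: mean proportion 0.8458; null SE 0.03525; alternative SE 0.02654; z = 2.635; power 0.996. This further assumes that all three later groups are assessed one week after starting ART, before the second group starts the game.

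**6. If the two rates are means of MPR.** MPR lies between 0 and 1, so its variance cannot exceed μ(1−μ), the binary variance used above. For a difference in mean of 0.139 with 140 per arm, 90% power needs a common SD no larger than 0.139 × √(140/(2×10.507)) = 0.36. The largest root-mean-square SD possible at means of 0.811 and 0.95 is √(0.20078/2) = 0.32. Power would therefore exceed 90%, provided that 0.139 is the right difference in mean MPR.

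**The case against.** The strongest defence is that nothing of substance changes. One minus sign restores the stated 140, so the authors evidently worked from a usable formula. The misprint may even come from text conversion, since other equations in the article are visibly damaged. The trial exceeds its 90% target for the stated contrast once the calculation is done for individuals. This stands: the sign is a reporting matter, and 140 was not invented.

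A reader might infer from the 152 and 165 per group that 700 is too few. The documents do not support that. Those figures come from a formula that does not apply to individual allocation, and the simple two-group calculation needs only 110 to 113 per arm.

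A reader might also set the six assessments per person listed in the text against the seven periods. Periods in a stepped wedge run over time shared by all groups, and the two design figures that would show them are not available. Only the mismatch between six steps and four start times is firm.

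Nor can the timing hypothesis be called underpowered by a definite amount. Any detectable difference depends on a choice of tests and a multiplicity rule that the Data analysis section does not make. An article may leave that to the analysis plan.

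Finally, the 95% and 99% figures rest on a binary endpoint. Outcomes and data collection defines MPR on a 0 to 1 scale with no cut-off, and Data analysis plans repeated-measures models. That caveat must travel with the figures. What the defence does not remove is that the printed inputs describe a different trial.

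**Conclusion.** The derivation is wrong as written. It is a cluster formula applied to individually randomised people, with arms in the place of clusters, a mislabelled correlation with no referent, and six steps where the design has four start times or fewer crossovers. The printed equation cannot be solved for a positive m, and the corrected one yields 140 only by rounding 20.45 down. Hence neither the 90% power nor the required 140 describes this design.

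No loss of power for the stated contrast is shown. Under the binary assumption at 81.1% versus 95%, 140 evaluable per arm gives about 95% between two arms, and over 99% for the first step group against the rest at week 1. Both figures depend on the assumed effect, on 20% loss and, for the second, on week-1 data in all four groups. The fault lies in the justification, not in the number enrolled.

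**What to change.** Keep 700. Replace the cluster calculation with one for individual randomisation to four arms, and restate the power as above with its assumptions: two-sided α of 0.05, 140 evaluable per group, 81.1% versus 95%. State either the adherence cut-off that makes the endpoint binary or the MPR standard deviation assumed. A detectable difference for the timing contrasts is optional; if given, label it as dependent on the chosen tests and multiplicity rule.

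If the cluster formula is retained for reference, correct its sign, use a t consistent with the four start times, call ρ the intracluster correlation and round m up.

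The cost is one rewritten paragraph, with no change to enrolment or procedures.

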### Randomization and allocation concealment

Opaque envelopes will be used for randomization. Among the 700 envelopes, each envelope contained a note with the words "First Step Group", "Second Step Group", "Third Step Group" and "Fourth Step Group" (175 envelopes per group). An opaque envelope will be selected for the first time the participant enrolled, and they will be assigned to the corresponding group according to the envelope. The health workers for the AIDS education of newly diagnosed young people with HIV and the data analysts will be blinded for the allocation.

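### As described, an envelope is picked at enrolment from a stock of 700 in no stated order and without regard to clinic, which leaves allocation open to steering; numbered varying blocks within clinic would close this cheaply.

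*Protocol article*

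**What the plan says.** The section on randomization and allocation concealment names the device ("Opaque envelopes will be used for randomization"), the stock ("Among the 700 envelopes, each envelope contained a note with the words" of one of the four step groups, with "175 envelopes per group"), and the act: "An opaque envelope will be selected for the first time the participant enrolled". The note inside then decides the group. Opacity is the only physical safeguard mentioned. On blinding, the section covers the health workers who give the AIDS education, and adds that "the data analysts will be blinded for the allocation". It does not say who takes the envelope.

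Study design makes allocation individual: "Participants will be assigned to the four groups in 1:1:1:1 randomly". Recruitment of participants puts enrolment at more than one site: "On-site recruitment will be conducted in AIDS clinics in Sichuan Province, China". The number of clinics is not given, nor how one set of 700 serves them. The intervention sections start the game at enrolment for the first step group, and one week, one month and three months after the start of ART for the other three.

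**The concern.** Picking from a set is a different procedure from opening the next envelope in a fixed order. With a fixed order, each participant is tied to one envelope before anyone knows its content. With a pick, a second envelope can be taken when the first is unwelcome, or two can be exchanged, and opacity prevents neither.

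The groups are easy to tell apart, since one begins the game at once and another waits three months. When to start is also one of the trial's own questions. If more motivated patients, or those thought ready, drifted towards particular groups, the comparison of start times would be distorted. A larger sample would not remove that distortion, and the analysis could not reliably repair it.

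The second, lesser matter is that nothing keeps the four groups balanced inside a clinic, where care and adherence support may differ.

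**Working it through.** **1. The plan's own figure.** From Sample size calculation: 140 per group with 20% loss. 140 / (1 − 0.20) = 175, and 4 × 175 = 700. The envelope stock matches the planned size.

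**2. Concealment.** No arithmetic applies; set the statements side by side.
- Stated: opaque envelopes, 700 in all, 175 per group, one selected at enrolment, education staff and analysts blinded.
- Not stated: order of use, sealing, who holds or takes the envelope, or a record made before opening.
- The text of Study design and Intervention design times assessments relative to the intervention, not to allocation. A baseline completed before the envelope is opened is therefore not assured for the later step groups. (Figures 1 and 2 were not available here and may show more.)

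Followed as written, the procedure allows a re-pick or a swap. How often that would happen cannot be derived. For scale only, with both inputs assumed: if motivated patients were 10 percentage points more common in one group, and their adherence was 20 to 30 points higher, the spurious difference would be 0.10 × 20 = 2 to 0.10 × 30 = 3 points. The planned effect is 95 − 81.1 = 13.9 points.

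**3. Balance within clinic under one pool.** Assume C equal clinics of n = 700/C, filled at random from the 4 × 175 labels. The SD of one group's count in a clinic is √[n × 0.25 × 0.75 × (700 − n)/699]. For 10 clinics of 70 this is √(13.125 × 630/699) = 3.4 around a mean of 17.5. Simulated draws give the gaps:

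| Clinics (assumed) | Size | Median gap, largest − smallest group | 95th percentile | Clinics with ratio ≥ 1.5 |
|---|---|---|---|---|
| 2 | 350 | 13 | 24 | 0.1% |
| 5 | 140 | 10 | 19 | 25% |
| 10 | 70 | 8 | 14 | 63% |
| 20 | 35 | 6 | 10 | 83% |

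With blocks of 4 in each clinic the gap is at most 1; with blocks of 8, at most 2.

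**4. What that imbalance costs.** For two groups compared within clinic, the information is Σ n₁n₂/(n₁+n₂), at most 175 × 175/350 = 87.5. Write n₁n₂/m = m/4 − (n₁ − n₂)²/(4m), where m = n₁ + n₂. Under one pool the expected squared difference is m(350 − m)/349. Summing over clinics, the expected relative loss is (C − 1)/349:
- 2 clinics: 1/349 = 0.3%
- 5 clinics: 4/349 = 1.1%
- 10 clinics: 9/349 = 2.6%
- 20 clinics: 19/349 = 5.4%

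Simulation agrees, with 99.7%, 98.9%, 97.4% and 94.6% of efficiency kept.

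If clinic is ignored, and the between-clinic SD in adherence is assumed to be 5 to 10 points, clinic mix contributes an SD of about 0.5 to 1.0 point to a group difference. The sampling standard error is √(2 × 0.811 × 0.189/175) = 4.2 points.

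**5. The price of blocking.** If staff know a fixed block of 4 and see each allocation, the expected share of correct guesses is (1/4 + 1/3 + 1/2 + 1)/4 = 52%. For blocks of 8 it is 47%, for blocks of 12 it is 44%, and for one counted pool of 700 about 28%. Block sizes should therefore vary and stay undisclosed.

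**The case against.** The strongest reply is that this is a four-sentence account in a journal article. Numbering, sealing, custody and distribution to sites are details an article commonly leaves to the full protocol, and selecting an envelope does not exclude taking the next one in a series. This stands in part. A reader might infer that the envelopes are unnumbered and that no audit trail exists; the article says neither, and silence does not establish it. What remains is that a section headed with concealment describes a pick from a stock and offers opacity as its only physical safeguard.

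A reader might also infer that imbalance within clinics biases the outcomes. It does not. Allocation is individual, the imbalance arises by chance, and the loss of precision is small. The share of clinics with a 1.5-fold ratio looks alarming, but it measures neither bias nor lost power, and it is near zero with two clinics. Unstratified randomisation of 700 people is acceptable.

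Two further replies have force. The education staff are said to be blinded, and every group eventually receives the game, so a motive to steer is plausible but not documented. Small blocks of known size would make the next allocation easier to guess, so stratified blocks are not free.

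**Conclusion.** The concern holds in a limited form. As described, the procedure does not prevent an envelope being re-picked or swapped, in a trial whose groups are visibly different and whose start times are themselves under study. No bias is shown, and its size cannot be derived from the document; the 2 to 3 points above rest wholly on assumed inputs.

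The lack of stratification by clinic is secondary. It costs roughly 1% to 5% of efficiency with 5 to 20 clinics, assuming equal clinic sizes and a single pool filled at random; the document gives neither the number nor the sizes. This is a cheap improvement to the stated method, not an error that invalidates the design. If the full protocol already fixes numbered, sealed envelopes used in order, the concealment half reduces to correcting the article's description.

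**What to change.** Before recruitment, replace the picking step with the following:
- A computer-generated list of permuted blocks within clinic, with block sizes varying in multiples of 4 and not disclosed to the sites.
- Release in fixed order, through sequentially numbered, sealed, opaque envelopes held as a separate set for each clinic, or through an electronic list if one is available. The data management system in the article is described only for monitoring game use, so it should not be assumed able to do this.
- Opening only after consent is signed and baseline data are recorded.
- Clinic as a factor in the GEE and mixed models already planned, to match the stratification.

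The cost is generating the list, preparing separate envelope sets and changing the enrolment step. The total stays at 700 with no added patients or staff, though group totals may miss 175 slightly where a clinic's last block is unfilled. Some predictability at block ends remains; varying, undisclosed sizes limit it but do not remove it.
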